### 7.2 Collected data

#### 7.2.1 Registry at the HDSS centre

Each patient visiting one of the designated study health facilities within the HDSS, suspected to have uncomplicated or complicated malaria, regardless of him/her being included in the study, will be recorded in a specific registry by the study team member who has examined him/her. The date of consultation, the age and sex of the patient, the village or neighbourhood he/she lives in, the recent history of any anti-malarial treatment intake, the weight, the clinical signs, the diagnosis, the prescribed treatment (dose and duration) will be reported in this document as well as the patient ID number (if recruited in the study) or the possible reason for not participating in the study. In this registry, for the patients included in the study, will be also reported the date on which the patient's chart was provided to the CHA (by the

HF) as well as the date in which the CHA consigned the filled in chart with data referring the follow-up contact at Day 5 ( $\pm 2$  days) at the HF; those dates will be reported for traceability purposes.

### 7.2.2 Examination and data collection at inclusion

In case the patient meets the protocol selection criteria and agrees to participate in the study, the following procedures will be followed:

- An informed consent form will have to be signed and will be filed with the registry.
- The HF will assign a patient ID number to the patient, visit the patient as usual and record the following data:
  - On the patient chart: last name, first name, full address (village/neighbourhood), registration number and patient ID number.
  - On the rest of patient chart: the other information collected during this visit, i.e.:
    - Demographic data of the patient: patient ID number, initials, age, sex, weight and body temperature.
    - Intake of anti-malarial drugs during the 4 weeks before inclusion.
    - Intake of any other treatment including traditional treatments, during the 2 weeks before inclusion.
    - Concomitant treatments and treatments prescribed when visiting the centre.
    - Malaria and associated disease symptoms will also be reported.
    - Confirmation that a thick blood smear identified by the patient's ID number and the date of blood withdrawal has been taken and prepared for later reading.
    - Confirmation that a blood sample for haematology, blood chemistry and PK (where foreseen) has been drawn in the subset of patients more closely evaluated; and that in the same subgroup a triplicate ECG has been recorded. Results of the ECGs local readings and laboratory examinations will be reported as soon as possible on the chart (copy of the results have to be stored at site).
    - Eurartesim® treatment administration time. Dosage will be defined according to the weight of the patient. The patient will be instructed to take the medication with water, between meals as described in section 5.3. In all the 10,000 patients the first dose of the study drug will be directly administered at the facility and time of administration and time of last food consumption will be annotated.

### 7.2.3 Follow-up visits/contacts and clinical tolerability follow-up questionnaire

At Day 5 ( $\pm 2$  days) (after administration of the last Eurartesim® dose) following the inclusion date, the community health agent (CHA) will contact the patient at home. A further visit at the patient's home will be scheduled by the community health agent in all the cases in which the information collected during the telephone contact should be considered incomplete or unreliable ones.

He/she will then fill-in the second part of the chart (in triplicate) and report:

- His/her own 4 digit identification number (first two digits are the number of the health centre he/she is attached followed by a 2 digit number which will be assigned to him/her when the study starts).
- Date of the visit/contact.
- Clinical condition (recovered status or continuation of the illnesses).
- Compliance with the prescribed Eurartesim® treatment and in case, number of tablets of Eurartesim® not taken; an explanation of the reason why the treatment was not followed should be provided.
- Description of the symptoms experienced by the patient in case of a positive answer to the question: *“Have you noticed any unusual event/symptom since your last visit at the centre?”* Collect date of first manifestation of this/these event(s), symptom(s), intensity, treatment dis-/continuation, and evolution, in the specific section of the patient chart dedicated to the collection of Adverse Events.
- Current treatments, if taken.

In case, during his/her contact, the CHA assess that an occurred event is serious and/or severe, or detects an adverse event of special interest (see section 8.5), he/she should contact the HA and transfer the patient to the health facility in order to be examined. If necessary in the opinion of the HA, he/she should contact the investigators so that they can visit the patient and exactly define the status of the event and the causality. If the adverse event belongs to the cardiovascular category, an ECG will be performed. In addition, a thick blood smear will be prepared (for future analysis). In that event, a specific adverse event report form will be completed by the HA or the investigators.

The patient will receive first care treatment. In case any other treatment is prescribed by a HA staff or the study doctor, it will be reported on the patient chart.

All the patients will be instructed to refer to the CHA or the designated HF in the HDSS should any adverse event occur within the 28 day after the start of the Eurartesim® administration.

In addition the regional hospital will be alerted to check referrals for participation in the study, and there will be a collection on a regular basis of any data related to patients who are treated in regional hospitals who have taken part in the study.

The patients recruited in the 1,000 subset group will be reviewed at the HF on day 3 (last day of administration of Eurartesim® dose). Before the Eurartesim® administration, a blood sample will be collected for PQ concentration evaluation (in all the 1000 subgroup of patients) and a single ECG will be recorded. The last dose of Eurartesim® will be directly administered by the HA to the patient after documentation that the last meal was taken more than 3 hours prior to administration. Three to four hours after the Eurartesim® administration, a blood sample for haematology, blood chemistry and PQ concentration will be collected and a triplicate ECG will be recorded.

The following information will be recorded in the second part of the chart (in triplicate):

- The HA or study team staff will record his/her own 4 digit identification number (number of the health centre he/she is attached followed by a 2 digit number which will be assigned to him/her when the study starts).
- Date of the visit.
- Clinical condition (recovered status or continuation of the illnesses).

- Time of drug administration
- Compliance with the Eurartesim® treatment during the three day treatment.
- Results of the ECGs and laboratory examinations
- Occurrence of Adverse Events.

The patients recruited in the subset will have to come back at the health facility on day 7 to perform a further single ECG, a blood sample drawing for haematology and biochemistry determinations and to collect, if any, Adverse Events occurred.

Again the HA or study team staff will record his/her own 4 digit identification number and record the appropriate information on the patient chart.

All the patients will be instructed to refer to the CHA or the designated HF in the HDSS should any adverse event occur starting from the 7 day visit/contact and the 28 day after the start of the Eurartesim® administration.

Female patients will be encouraged to communicate to the study team if they get pregnant within a period of two months after the start of the Eurartesim® treatment. In these cases, information on the evolution of the pregnancy will be collected at 3, 6, 9 months and after the delivery (6 and 14 weeks). Information on the drugs taken during the pregnancy as well as AEs/SAEs/AESIs and the health status of the newborn/s will be collected and reported in the patient chart.

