#### 3.2 Eurartesim®

Eurartesim® is a fixed-dose combination product composed of dihydroartemisinin (DHA) and piperaquine phosphate (PQP) for the oral treatment of uncomplicated *Plasmodium falciparum* malaria. Eurartesim® contains DHA, to which all malaria strains are susceptible and to which drug resistance has not been reported. The long-term efficacy of Eurartesim® is secured by the presence of PQP. PQP is a second anti-malarial compound with a different mechanism of action and much longer half-life. Eurartesim® appears to offer significant benefits over existing licensed malaria treatments and is in line with current WHO treatment policy recommendations.

Two pivotal trials on the efficacy of Eurartesim® on treatment of uncomplicated *Plasmodium falciparum* malaria have been conducted in Africa and Asia, showing a high rate (>95 %) of treatment success. The Eurartesim® registration dossier has been submitted to EMA authorities and it got a centralized marketing authorization.

Evaluating possible drug-related side effects in patients with malaria and treated in the endemic countries can be difficult. There is considerable overlap between treatment-related symptoms and signs, and those of malaria (such as fever, anaemia) and concomitant illnesses (such as viral infections and parasitic infestations). Other reported AEs have been headache, vomiting, abdominal pain, asthenia, and cough.

The potential for Eurartesim® to prolong the QTc interval was investigated in parallel groups of healthy volunteers co-administered with high (~1,000 Kcal) or low (~400 Kcal) fat/calorie meals or in fasting conditions. Compared to placebo, the maximum mean increases in QTcF following Eurartesim® administration were 45.2, 35.5 and 21.0 msec, respectively, on day 3. Such QTcF prolongation observed under fasting conditions lasted between 4 and 11 hours after last dosing on day 3; afterwards, the mean QTcF prolongation compared to placebo decreased to 11.8 msec at 24 hours and to 7.5 msec at 48 hours. No healthy subject dosed in fasting conditions showed a QTcF greater than 480 msec, or an increase over baseline greater than 60 msec. The number of subjects overpassing these thresholds were 3 and 10 out of 64, respectively, for the low fat/calorie condition and 3 and 14 out of 40 for the high fat/calorie

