All patients visiting one of the health facilities referring to the HDSS centres and for whom a diagnosis of uncomplicated malaria (according to the WHO criteria) is suspected or confirmed by a parasitological diagnosis will be enrolled in the study after their informed consent (a parent's or guardian's consent form **signature will be required for children as per each country regulation**) has been obtained. For teenagers (age depending on country regulations), an assent to participate in the study will be also sought if required by the National guidelines. A thick blood smear will be prepared for microscopic diagnosis. **For the participants consented into the main group, eurartesim® tablets will be prescribed to the patients (or to the parents/guardians if the patients are children) meeting the protocol inclusion criteria before the results of the thick blood smear are known if malaria has already been confirmed from RDT and/or clinical examination as per country regulations.**

The patients will be contacted at Day 5 ( $\pm$  2 days) by a community health agent (CHA) of the HDSS, in order to capture recovery status and all the experienced adverse events. A visit by the community health agent will be scheduled on all the cases in which the information collected during the telephone contact should be considered incomplete or unreliable ones. Special procedures will be followed in case of serious and/or severe adverse events and events classified of special interest (see specific section).

The subset of 1,000 patients will be intensively followed-up. These patients will have haematology (Hb and full blood counts (RBC, WBC and WBC differential count)) and standard biochemistry (BUN, Creat, ALT/AST, Bilirubine, electrolytes (K+ and Cl)) undertaken at Day 1 (before drug administration), Day 3 (3-4 hours after the last dose of treatment), and Day 7.

**Each blood sampling for both haematology and biochemistry requires about 2mL of venous whole blood. This makes up for a total amount of about 6mL of venous whole blood to be taken from each participant in the nested group for the entire study period.**

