#### 5.4 Evaluation criteria

Primary evaluation criterion: The clinical safety of Eurartesim® will be evaluated through the analysis of the adverse events captured by the health agent that will contact each patient at Day 5 ( $\pm 2$  days) after starting of Eurartesim® treatment. Any AE referred (frequency, intensity, action taken, outcome) will be recorded on the specific section of the patient chart as well as those identified in the referring hospitals or through adverse events spontaneously reported by the patient detected at the health facility within 28 days after the first medication intake. Special attention will be given to the serious adverse events (SAE) and/or adverse events (AE) classified as severe and/or adverse events of special interest (AESI) (see section 8.5).

- Main secondary evaluation criteria: The cardiac and biological safety of Eurartesim® will be intensively evaluated in the nested subset of **about 1,000** patients to evaluate the effect of the administration of Eurartesim® on blood biochemistry (BUN, Creat, ALT/AST, Bilirubin, electrolytes (K+ and Cl)), full blood count (Hb, RBC, WBC and differential count)) as well as ECG parameters. In case of clinically significant abnormalities, the examination will be repeated. The occurrence of adverse events will be recorded during these visits. Concentrations of PQ will be evaluated in a subgroup of about 200 patients at baseline (Day 1 before drug administration), Day 3 (before the last drug administration and 3-4 hours after the last drug administration), and Day 7. QTc interval and piperaquine concentration relationship will also be investigated.

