### **8.4 Obligation of AE notification**

#### ***Adverse Events***

The AEs, regardless of their seriousness and causal relationship to the study drug, arising between the signature of the informed consent form and the last study visit (as per the protocol), must all be recorded on the patient chart (AE recording section). When possible, the symptoms must be regrouped within a single syndrome or diagnosis. The healthcare personnel shall have to specify the date of manifestation of the event, its intensity, final evolution, the measures taken and the treatment undertaken (if any).

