### **9.2 Analysis in the whole sample**

#### **Analysis in the whole sample and in the Subset population**

The statistical analysis will be mainly descriptive. The estimates of the incidence of adverse events will be based on crude rates. All estimates will be complemented with appropriate 95% confidence intervals.

The adverse events shall be regularly coded using MedDRA before database lock.

All SAEs and AESIs will be reviewed centrally by an independent safety monitoring panel.

Incidences will be computed on the following classes of AEs, overall and by SOC/PT:

- All AEs
- Serious AEs
- Serious AEs related to study treatment
- AEs of special interest (AESIs)
- AEs which caused early discontinuation of Eurartesim®
- AEs related to Eurartesim® treatment

Specific analyses will be carried-out on the AESIs. Correlation analyses will be carried-out in order to verify if their occurrence is more frequent with the previous/concomitant use of other drugs (specific classes to be determined in the statistical analysis plan), including antimalarials, in presence of co-morbidity (specific classes to be determined in the statistical analysis plan), or in presence of parasitaemia.

Compliance will be computed in the whole population and in the subset of **about 1,000** patients, calculating for each patient the ratio between the number of tablets taken and the number of tablets that the patient should have taken. Two groups of patients shall be described: compliant = 100% treatment compliance and non compliant = other cases. The safety profile of compliant vs non-compliant patients will be compared.

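### The Day 5 question in 7.2.3 and the self-report instruction in 7.1 ask only about unusual symptoms, which is narrower than the all-adverse-event scope of 5.1, 7.2.3 and 8.4 and may bias main-group incidence low

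*Protocol*

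**What the plan says.** Section 5.1 states the purpose of the Day 5 contact: patients are reached "in order to capture recovery status and all the experienced adverse events". Section 8.4 sets the recording duty: adverse events, whatever their seriousness or cause, "must all be recorded on the patient chart (AE recording section").

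Section 7.2.3 lists what the community health agent writes down at that contact. The adverse-event item reads "Description of the symptoms experienced by the patient in case of a positive answer to the question", and the question is then given verbatim: "Have you noticed any unusual event/symptom since your last visit at the centre".

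The 28-day self-report is worded in two ways. Section 7.1 asks patients to come forward for a symptom that is both unusual and significant. Section 7.2.3 tells them to come forward for any adverse event.

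Under 5.4 the primary criterion rests first on "adverse events captured by the health agent that will contact each patient at Day 5", and adds those "identified in the referring hospitals or through adverse events spontaneously reported by the patient detected at the health facility within 28 days". Section 9.2 (Analysis in the whole sample and in the Subset population) fixes the estimator: "The estimates of the incidence of adverse events will be based on crude rates".

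**The concern.** All and unusual are different thresholds. The protocol sets the first as its scope and puts the second into the question its field staff must ask. Because the description of symptoms depends on a yes, an event that the patient regards as ordinary does not reach the adverse-event section of the chart through this item.

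The direction is foreseeable. Section 3.2 says that drug effects overlap considerably with the signs of malaria and of concomitant illness, and it names the familiar complaints: "Other reported AEs have been headache, vomiting, abdominal pain, asthenia, and cough". A patient treated for malaria a few days earlier can truthfully say that a headache or a cough is nothing unusual.

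At stake are the all-event and drug-related incidences in the main group. Section 8.2 has the investigator's team judge causality from the events on the chart, so an event filtered out at the contact never gets that judgement. No later analysis can restore an event that was not recorded.

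**Working it through.** **Step 1. Set the passages side by side.**

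| Place | Event or channel | Threshold |
|---|---|---|
| 5.1 | Purpose of the Day 5 contact | all adverse events |
| 8.4 | Recording duty | all, whatever seriousness or cause |
| 7.2.3, 28-day instruction | Self-report | any adverse event |
| 7.2.3, Day 5 question | Active contact | unusual |
| 7.1 | 28-day self-report | unusual and significant |

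The last two rows are narrower than the first three. The fourth row is the main source of the primary criterion in 5.4.

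**Step 2. The plan's own figures.** Section 9.3 claims a 95% probability of seeing an event with incidence 1/3,000 in about 10,000 patients. The formula is P(at least one) = 1 − (1 − p)^n.
- n = 10,000: 1 − (1 − 1/3,000)^10,000 = 0.964.
- n = 9,000: 0.950.

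The claim reproduces and is not in dispute.

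**Step 3. What incomplete capture would do to a common event.** Let t be the true incidence of events that qualify as adverse events under 8.3. Let s be the share of them that is recorded by any route: the question, hospital reports or spontaneous reports. Defined this way, s already leaves out excluded malaria signs and already credits the other channels. The expected crude estimate is t × s, the bias is t × (1 − s), and the 95% half-width is 1.96 × √(ts(1 − ts)/n). The main-group size n = 9,000 comes from 7.3.1. The documents give neither t nor s, so both are assumptions shown over a range.

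| t (assumed) | s = 0.9 | s = 0.7 | s = 0.5 |
|---|---|---|---|
| 5% | 4.5% (4.1 to 4.9) | 3.5% (3.1 to 3.9) | 2.5% (2.2 to 2.8) |
| 10% | 9.0% (8.4 to 9.6) | 7.0% (6.5 to 7.5) | 5.0% (4.5 to 5.5) |
| 20% | 18.0% (17.2 to 18.8) | 14.0% (13.3 to 14.7) | 10.0% (9.4 to 10.6) |

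The interval excludes t in every cell. With t = 10% and full capture the half-width is 1.96 × √(0.1 × 0.9/9,000) = 0.62 points. At s = 0.94 the bias is 10% × 0.06 = 0.60 points and the half-width is 1.96 × √(0.094 × 0.906/9,000) = 0.60 points. Below that share, bias exceeds sampling error.

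**Step 4. Rare events.** If s applied to the 9,000 and capture in the nested 1,000 were complete, P(at least one) = 1 − (1 − s/3,000)^9,000 × (1 − 1/3,000)^1,000. This gives 0.952 at s = 0.9, 0.912 at 0.7 and 0.840 at 0.5. The low values of s are implausible for serious or striking events, which few patients would call ordinary. The concern therefore lies mainly with mild, familiar events.

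**The case against.** Four points on the other side carry weight.

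- **Section 8.3 already excludes signs typical of acute malaria** unless healthcare personnel find them exceptional. Some no answers will therefore concern symptoms that would not have counted. That stands and reduces any loss. It does not remove it: 8.3 gives the judgement to staff, whereas the question lets the patient make it first, and what seems usual is not limited to malaria.
- **The question is not the only source.** The same contact records clinical condition, reasons for missed tablets and current treatments. A home visit follows when telephone information is incomplete or unreliable. Hospital and spontaneous reports count, and the whole-sample flow chart marks adverse-event recording at unforeseen visits and at the end of the 28 days. This also stands. However, hospital and spontaneous reports mainly pick up events that lead someone to seek care, and the other Day 5 items are not adverse-event queries.
- **Open questioning is deliberate.** Section 8.1 trains staff in it. True, but an open question does not need the word *unusual*.
- **The sample size is aimed at rare events**, and 5.4 gives special attention to serious, severe and special-interest events. These are the least exposed. Even so, 9.2 also reports incidence for all adverse events and for related ones.

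A reader might infer more than the documents support:

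- That the reference to the last visit loses events when a patient came back before Day 5. The flow chart provides for recording at unforeseen visits, so the question continues from there and no loss is shown.
- That main-group and nested rates are demonstrably collected on different terms. Section 5.1 says events are solicited on Days 3 and 7 in the subset, but no wording is given and 9.2 plans no comparison of the two groups.
- That the effect differs between sites through translation. Nothing in the protocol shows this.

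**Conclusion.** The mismatch in wording is plain from the text: the Day 5 question in 7.2.3 and the instruction in 7.1 are narrower than 5.1, 8.4 and the 28-day instruction in 7.2.3. Its consequence is a possibility with a clear direction. Mild or familiar events may go unreported in the roughly 9,000 main-group patients, and the crude all-event and related-event incidences may be biased low.

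It would go too far to say that such events are missed, or that the incidences are biased by a stated amount. The documents give no capture share, and the figures above only follow from assumed values of t and s. They do show that with 9,000 patients a modest loss, about 6% of events at an assumed incidence of 10%, would match the sampling error, and that a large sample does not protect against it. No sample-size figure changes. The point is worth correcting because the remedy is small and lost reports cannot be recovered afterwards.

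**What to change.** - **7.2.3, Day 5 question:** keep a single open, non-leading question and drop the threshold. For example: *Have you (has your child) had any new or worsened symptom or health problem since the first dose?* The first dose is given at the facility on Day 1 and onset dates are collected, so events already noted at an unforeseen visit can be matched.
- **7.1:** replace the restriction to unusual and significant symptoms with any adverse event, as 7.2.3 already says for the 28 days.
- **Nested visits on Days 3 and 7:** state that the same question is used.
- **8.3:** leave the malaria-sign judgement with the healthcare personnel, applied after the symptom has been recorded.

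The cost is one line on the chart, retranslation into the local languages and a training note. The real downside is more non-serious reports to review and code, including malaria symptoms that staff will then set aside under 8.3.
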